### 2.6. Questionnaire Survey

A parental questionnaire consisting of three parts (the child’s basic information, dietary and oral hygiene habits, and family demographic characteristics) will be administered at the baseline and final follow-up visits. It will be used to collect information, including daily tooth brushing, frequency of snack intake, whether parent-assisted tooth brushing is used, whether a child is bottle-fed before sleeping without tooth brushing or mouth rinsing, use of fluoride toothpaste, parental satisfaction with the child’s oral health and appearance, the child’s main caretaker, parental education level, and monthly family income. For the 12-month follow-up period, information on children’s dental treatment experiences will also be included. In addition, a questionnaire about adverse effects, such as systemic toxicity, vomiting, and hospitalization, will be collected after SDF treatment. The grouping of the categorical variables of the questionnaire at baseline and at the 12-month follow-up are summarized in Table 3.

### 2.7. Randomized Allocation, Concealment, and Blinding

This trial will use the stratified randomization method to allocate children randomly into two intervention groups. The recruited children will be firstly distributed into two strata based on their dental caries experiences to achieve balance in the disease severity among the two groups. Children with one to three caries surfaces will be stratified into low-caries group. Children with four or more caries surfaces will be stratified into high-caries group. Then, children in each stratum will be randomly allocated into one of the two treatment groups based on the random number with a block size of six generated by the Excel software.

An assistant who will not participate in the dental examination or treatment intervention will generate the allocation sequence. After the children receive the SDF treatment, the assistant will then open the concealed label to identify the group allocation. The participants know their treatment interventions, but the examiners are blinded and do not know the treatment allocation.

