### 2.8. Interventions

All the tooth surfaces with carious lesions will be treated with 38% SDF (Advantage Arrest Elevate Oral Care, FL, USA) solutions. The SDF application will be adopted from the recommended clinical procedures [26] as follows: remove food debris, isolate the decayed tooth with a gauze or cotton roll, and apply SDF with a microbrush on the decayed tooth for 60 s. After SDF treatment, one assistant who helps teachers instructs children to comply with various post-treatment protocols will allocate children to one of the two intervention groups. The dentist will not know the group allocation. The following are the two post-treatment protocols. Children in Group A will be instructed to rinse their teeth with a cup of about 50 mL of water immediately after SDF treatment. Afterward, no post-treatment instruction is given to the children. Children in Group B will be instructed not to rinse, eat, or drink for 30 min.

A research assistant will record and monitor the children’s compliance with the intervention in each group at each treatment visit. The intervention will be conducted at baseline and at the 6-month follow-up. All examinations and interventions will be conducted in school settings.

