### 2.10. Sample Size Calculation

According to the published studies, approximately 70% of active dentine caries in primary teeth were halted after 38% SDF treatment [27]. Clinical significance would be defined as an absolute difference of 10% in the arrested caries rate between the groups. A two-tailed test with a statistical significance of 0.05 (α = 0.05) and a power of 80% (β = 0.2) will be set. The Sealed Envelope website will be used to calculate the sample size (https://www.sealedenvelope.com/, accessed on 1 November 2022). At least 708 active carious tooth surfaces in total (354 per group) are needed.

The anticipated intraclass correlation coefficient for the caries data at the tooth surface level within a child is 0.13. Following the results of the published study, the mean number of decayed tooth surfaces per child was 5 at baseline. According to the sample size calculation for a multilevel statistical model, the estimated design effect is 1.52. Hence, at least 1077 decayed tooth surfaces are needed. After 12 months, the anticipated dropout rate is approximately 15%. Therefore, at least 1267 tooth surfaces and 254 children in total (127 per treatment group) need to be recruited at baseline.

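### On its natural reading, Section 2.7 has the assistant who generates the allocation sequence also open the concealed labels, and Section 2.8 does not fit the role Section 2.7 describes

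*Protocol article*

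**What the plan says.** Section 2.7 of the protocol article describes stratified randomization in two caries strata, "based on the random number with a block size of six generated by the Excel software". It then assigns two tasks in consecutive sentences. The first reads: "An assistant who will not participate in the dental examination or treatment intervention will generate the allocation sequence". The second reads: "After the children receive the SDF treatment, the assistant will then open the concealed label to identify the group allocation".

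Section 2.8 describes the same moment, after SDF application, in different terms: "one assistant who helps teachers instructs children to comply with various post-treatment protocols will allocate children to one of the two intervention groups". It separately mentions a research assistant who records compliance.

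The safeguards are also stated. In Section 2.8: "The dentist will not know the group allocation". In Section 2.7: "the examiners are blinded and do not know the treatment allocation". The article does not say how many people the various assistants are, and names no other person who holds or opens the labels.

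**The concern.** Concealment means that whoever links a child to a group cannot know the group beforehand. A label hides the group from the dentist and the examiners, but not from the person who produced the list behind it. If the generator opens the labels, the safeguard is missing at the one step where it is needed.

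The setting gives some reason to care. The Discussion says the 30-minute restriction is hard to run near lunch or break time and sometimes disturbs the school schedule. Someone who knew the next label could, if free to do so, match particular children to particular labels. If those children differed in ways related to caries arrest, the groups would differ from the start, and blinded examination at 12 months could not correct that.

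**Working it through.** No stated figure depends on this point, so the main check compares the two sections.

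**Step 1. Who opens the label (Section 2.7).** The sentence on label opening uses the definite article. The only assistant introduced up to there is the generator, one sentence earlier. On its natural reading, Section 2.7 alone therefore gives generation and label opening to one person.

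**Step 2. What the randomized intervention is.** Both groups receive the same 38% SDF. They differ only in what follows, which Section 2.8 introduces with "The following are the two post-treatment protocols". Table 1 lists Groups A and B under interventions. Helping to give the instruction is therefore taking part in the intervention under test.

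**Step 3. Who allocates (Section 2.8).** The allocating assistant helps with that instruction. There are two cases:
- Same person as in Section 2.7: the generator takes part in the intervention, contrary to the first sentence quoted from Section 2.7.
- Different person: Section 2.7 has the generator identify the group and Section 2.8 has someone else allocate. The sections then disagree, and by Section 2.7 the generator still opens the labels.

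**Step 4. What is already fixed when the label is opened.** By then the child has parental consent (Section 2.3), has been screened (Section 2.5.1), has been placed in a stratum (Section 2.7) and has been treated with SDF by a dentist unaware of the group (Section 2.8). Only the match of child to label remains open.

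**Step 5. Extent of foreknowledge.** The number of assignments is the planned 254 (Section 2.10), which reproduces from the stated inputs:
- Design effect: 1 + (5 − 1) × 0.13 = 1.52.
- Surfaces: 708 × 1.52 = 1076.2, rounded up to 1077.
- After 15% dropout: 1077 / 0.85 = 1267.06, given as 1267.
- Children: 1267 / 5 = 253.4, rounded up to 254.

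A generator who keeps the list could know all 254.

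For comparison, take someone who did not generate the list but knows the block size and every earlier assignment in the stratum. A block of six with three per group has 6!/(3! × 3!) = 20 equally likely sequences.
- Certain assignments are those left once one group is used up, that is, the final run of the block. It has length 1 in 12 sequences, length 2 in 6 and length 3 in 2. The mean is (12 × 1 + 6 × 2 + 2 × 3) / 20 = 1.5 of 6, or 25%.
- Guessing the group with more places left, and tossing a coin when they are equal, gives on average 4.1 of 6 correct, or 68.3%, against 50% by chance.

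**The case against.** The strongest reply is that this is loose wording in a condensed article. The identity of the assistants in the two sections is inferred. The phrase in Section 2.7 about examination and treatment could mean only the dentist's work, in which case an assistant who opens labels and relays an instruction breaks no stated rule. The label is opened late, after everything listed in Step 4. Nothing says that the assistant controls the order of children, and nothing links cooperation or time of day at the visit to arrest at 12 months. The remark about lunch concerns the outreach service, not assignment in this trial. A stated block size of six in two strata is ordinary practice.

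Much of this stands. A reader might infer that one person demonstrably creates, knows and applies the whole list, that this person can choose which child comes next, and that the primary comparison is therefore biased. The documents do not support that: the single identity is not stated, control of the order is not described, and no bias is shown. Nor do they suggest selective enrolment, unequal SDF application or failed blinding of outcome assessment.

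Two things survive. First, the narrow reading of treatment makes the sections consistent only by letting the same assistant generate the list, open the labels and allocate, which is the concealment weakness itself. Second, this is not a detail left to a fuller document: the article states the roles, and as stated they do not fit together. The block size is secondary. Varying it would do nothing against a person who holds the list.

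**Conclusion.** The point holds in a limited form. As Section 2.7 is written, allocation is not concealed from the person who reveals it, and Sections 2.7 and 2.8 need to be reconciled on who generates, holds and opens the labels and who allocates. The first conclusion rests on reading the assistant who opens the label as the generator, which is the natural reading but could be a drafting slip. The contradiction over taking part in the intervention needs two further assumptions: that the assistants of the two sections are one person, and that the instruction counts as the intervention.

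The exposure is confined to matching children to labels after SDF application. Foreknowledge could reach all 254 assignments if the generator keeps the list. For a non-generator tracking a stratum it would be 25% certain and 68.3% guessable. These figures measure predictability, and none is an estimate of bias in the arrest rate. The sample size is unaffected. The change is worth making because it is cheap and removes the exposure, but the documents do not show that the trial's result is compromised.

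**What to change.** For children not yet allocated:
- Have an existing team member with no role in label opening, allocation, instruction, examination or analysis generate and seal the list. The analyst should not be the generator, since that would give the analyst the allocation key.
- Have the on-site assistant open the next numbered label for the child's stratum, in order of treatment.
- Reword Sections 2.7 and 2.8 so that both name the same roles for generating, holding and opening the labels and for allocating.

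For children already allocated, state in the trial report who carried out each step. Section 2.12 has recruitment starting in February 2023 and ending in June 2023, so this may be the larger part of the remedy.

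Varying the block size is an optional secondary measure against someone who tracks a stratum.

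The cost is the reassignment of one task within the team, assuming a member without those roles is available (the article gives no staffing list), and a few sentences of text. Sample size, visits and outcome assessment do not change.

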### 2.8. Interventions

All the tooth surfaces with carious lesions will be treated with 38% SDF (Advantage Arrest Elevate Oral Care, FL, USA) solutions. The SDF application will be adopted from the recommended clinical procedures [26] as follows: remove food debris, isolate the decayed tooth with a gauze or cotton roll, and apply SDF with a microbrush on the decayed tooth for 60 s. After SDF treatment, one assistant who helps teachers instructs children to comply with various post-treatment protocols will allocate children to one of the two intervention groups. The dentist will not know the group allocation. The following are the two post-treatment protocols. Children in Group A will be instructed to rinse their teeth with a cup of about 50 mL of water immediately after SDF treatment. Afterward, no post-treatment instruction is given to the children. Children in Group B will be instructed not to rinse, eat, or drink for 30 min.

A research assistant will record and monitor the children’s compliance with the intervention in each group at each treatment visit. The intervention will be conducted at baseline and at the 6-month follow-up. All examinations and interventions will be conducted in school settings.

### 2.9. Outcome Measure

#### 2.9.1. Primary Outcome

The primary outcome measurement will be the proportion of caries lesions that become arrested at the 12-month examination.

#### 2.9.2. Secondary Outcome

Parental satisfaction about their child’s teeth appearance and oral health status will be evaluated prior to the baseline examination and at the 12-month examination. The SDF treatment’s adverse effects will also be assessed after SDF application.

### 2.10. Sample Size Calculation

According to the published studies, approximately 70% of active dentine caries in primary teeth were halted after 38% SDF treatment [27]. Clinical significance would be defined as an absolute difference of 10% in the arrested caries rate between the groups. A two-tailed test with a statistical significance of 0.05 (α = 0.05) and a power of 80% (β = 0.2) will be set. The Sealed Envelope website will be used to calculate the sample size (https://www.sealedenvelope.com/, accessed on 1 November 2022). At least 708 active carious tooth surfaces in total (354 per group) are needed.

The anticipated intraclass correlation coefficient for the caries data at the tooth surface level within a child is 0.13. Following the results of the published study, the mean number of decayed tooth surfaces per child was 5 at baseline. According to the sample size calculation for a multilevel statistical model, the estimated design effect is 1.52. Hence, at least 1077 decayed tooth surfaces are needed. After 12 months, the anticipated dropout rate is approximately 15%. Therefore, at least 1267 tooth surfaces and 254 children in total (127 per treatment group) need to be recruited at baseline.

### 2.11. Data Analysis

An assistant will enter the collected data into the Excel file and then proofread the data entry. The proofread data will be imputed to IBM’s SPSS 26.0 software (IRB Corp., Armonk, NY, USA) for statistical analysis. Cohen’s Kappa test will be employed to test the intra-examiner agreement for caries assessment. A statistical significance level will be set at 0.05 for all tests.

Chi-square (χ^2^) test will be conducted to assess the differences between the two intervention groups regarding their demographic background (sex, birthplace, family monthly income, parental education levels), their baseline clinical features (caries extent, tooth type, presence of dental plaque on decayed tooth surfaces), and their oral health-related habits (use of fluoride toothpaste and snacking). The baseline differences in VPI value and dmfs value between the two groups will be analyzed using a *t*-test. A logistic regression model will be used to assess the associations between the outcomes and other potential factors.

Regarding the clustering effect, because one child may have more than one untreated carious tooth surface, the lesions in the same child may be correlated. Therefore, two-level (subject level and tooth surface level) generalized estimating equation models will be used to assess the independent variables associated with the effectiveness of post-treatment protocols in arrested caries after 12 months. The independent variables include the children’s demographic information (sex, birthplace, family monthly income, parental education levels), their baseline clinical features (caries extent, tooth type, presence of dental plaque on decayed tooth surfaces, caries experience, and oral hygiene status), and children’s oral health-related behaviors (use of fluoride toothpaste, type of bottle feeding, and snacking habits). The McNemar test will be used to investigate changes in parental satisfaction regarding their child’s oral health and appearance at baseline and at the 12-month examinations.

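### Chi-square tests on three lesion-level baseline features ignore within-child correlation, and a separate logistic regression sentence leaves room for an unclustered analysis of arrest

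*Protocol article*

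**What the plan says.** All of this is in the protocol article.

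- **Baseline comparisons (2.11).** Chi-square tests compare the two groups on demographics, on oral health habits and on "their baseline clinical features (caries extent, tooth type, presence of dental plaque on decayed tooth surfaces". No adjustment for several lesions per child is attached to these tests. The significance level is 0.05 for every test.
- **Logistic regression (2.11).** In the same paragraph: "A logistic regression model will be used to assess the associations between the outcomes and other potential factors". Unit of analysis, outcome and variance method are not given.
- **GEE (2.11, next paragraph).** The article recognises that lesions of one child may be alike. For that reason it assigns arrest at 12 months to two-level GEE models with a listed set of covariates.
- **Level of measurement (2.5.2 and Table 2).** Extent and plaque are recorded for each carious tooth surface. Tooth type belongs to the tooth, so it too can differ between lesions of one child.
- **Randomisation (2.7).** Children are allocated, in strata of one to three and of four or more carious surfaces.
- **Clustering (2.10).** "The anticipated intraclass correlation coefficient for the caries data at the tooth surface level within a child is 0.13". With a mean of 5 surfaces per child, the design effect is 1.52.
- **Outcomes (2.9).** The primary outcome is arrest of lesions. The secondary outcomes are parental satisfaction and adverse effects, which relate to the child.

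**The concern.** A Pearson chi-square test assumes independent observations. On about 1,267 surfaces from 254 children, with group assigned by child, that assumption fails to whatever extent lesions of one child resemble each other. The plan quantifies this resemblance for its sample size and corrects for it in the GEE, but not in the three lesion-level baseline comparisons. Chance imbalances would be declared significant more often than the stated 5%.

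The logistic regression sentence raises a related risk. It stands apart from the clustering paragraph and refers to outcomes without limit, and the primary outcome is a surface-level one. An analyst following it literally could fit an unclustered model to arrest and have two sets of p-values for the same associations. For child-level factors such as income, parental education or snacking, the unclustered set would be too optimistic.

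**Working it through.** **1. The plan's own figures.** Inputs from 2.10: two-sided alpha 0.05, power 80%, arrest rate 70%, difference 10 points, intraclass correlation (ICC) 0.13, 5 surfaces per child, dropout 15%. The direction of the difference is not stated; 70% against 60% reproduces the stated size.

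- Surfaces per group: (1.960 + 0.842)² × (0.7×0.3 + 0.6×0.4) / 0.10² = 353.2, so 354, and 708 in total.
- Design effect: 1 + (5 − 1) × 0.13 = 1.52.
- 708 × 1.52 = 1076.2, so 1077.
- 1077 / 0.85 = 1267.06, stated as 1267.
- 1267 / 5 = 253.4, so 254 children.

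The figures reproduce, so 1.52 is a fair statement of the clustering that the plan expects for its caries data.

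**2. Error of an unclustered test on a child-level factor, such as group.** The naive standard error is 1/√DE of the correct one, where DE is the design effect, and the true size of a nominal 5% test is 2 × [1 − Φ(1.96/√DE)].

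- √1.52 = 1.233, and 1/1.233 = 0.811, so the standard error is about 19% too small.
- 1.96/1.233 = 1.590, which gives a type I error of 0.112.

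**3. Sensitivity to the ICC.** The 0.13 is stated for the caries data. The documents give no value for extent, tooth type or plaque at baseline.

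| ICC (assumed) | Design effect, 5 surfaces each | Type I error |
|---|---|---|
| 0.05 | 1.20 | 0.074 |
| 0.13 | 1.52 | 0.112 |
| 0.20 | 1.80 | 0.144 |
| 0.30 | 2.20 | 0.186 |

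**4. Sensitivity to unequal lesion counts.** The strata in 2.7 show that counts vary, but no coefficient of variation (CV) is given, so 0 to 1 is assumed. With DE = 1 + [(1 + CV²) × 5 − 1] × 0.13:

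| CV (assumed) | Design effect | Type I error |
|---|---|---|
| 0 | 1.52 | 0.112 |
| 0.5 | 1.68 | 0.131 |
| 0.75 | 1.89 | 0.154 |
| 1.0 | 2.17 | 0.183 |

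**5. Simulation.** There were 20,000 replicates of beta-binomial data with 216 children (254 × 0.85 = 215.9), a mean of 5 surfaces, ICC 0.13 and a proportion of 0.7.

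| Setting | Unclustered test | Cluster-robust variance |
|---|---|---|
| Child-level factor, 5 surfaces each | 0.113 | 0.052 |
| Child-level factor, variable counts | 0.156 | 0.056 |
| Factor varying within the child | 0.038 | not run |

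The first row confirms the formula, and a variance of the GEE type brings the size back close to 5%. The last row shows that the direction reverses for a regression covariate that varies among lesions of one child. That reversal does not rescue the three baseline tests: there the factor is group, which is fixed within a child, so a positive ICC in the feature inflates the error.

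**The case against.** The strongest reply is that clustering is handled where it matters. The sample size is inflated for it, 12-month arrest goes to a two-level GEE expressly because of it, and no chi-square test of arrest is planned. All of this stands.

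A reader might infer that the treatment comparison itself runs at 11% type I error. The documents do not support that: 2.11 assigns effectiveness to the GEE, and the logistic regression sentence speaks of other factors without naming group.

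A reader might also take the logistic regression to be an ordinary surface-level model. The text does not say so. It could serve child-level outcomes, or simply announce the logit model that the GEE then fits. Neither reading is stated, however. Parental satisfaction already has a McNemar test for change and is collected in four categories, so it is not an obvious target for a binary model; and if the sentence only previews the GEE, it is redundant. The ambiguity stands; a proven error does not.

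Most of the chi-square variables (sex, birthplace, income, parental education, toothpaste, snacking) have one value per child and need no adjustment. The affected baseline tests carry no treatment inference, and the GEE covariates are listed in advance, so a spurious imbalance would not alter the stated model. These points limit the consequence but do not make the three tests valid. An article may leave detail to a fuller document, but here it names a specific test for lesion-level features.

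**Conclusion.** The point holds in a limited form. Three baseline comparisons are assigned a test that does not suit their data: about 11% type I error for a nominal 5%, if the plan's ICC of 0.13 and 5 surfaces per child apply to them. Over assumed ICCs of 0.05 to 0.30 the range is about 7% to 19%, and unequal lesion counts would raise it further. This rests on the tests being run on lesions or surfaces, as the features are recorded, and on a positive ICC.

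Separately, the logistic regression sentence as worded permits an unclustered analysis of arrest beside the GEE. If it were run that way, standard errors for child-level factors would be about 19% too small. A general statement that p-values would be too small goes beyond the evidence, because tests of within-child factors can be conservative (0.038 in the simulation).

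The effect is on the baseline table and possibly on reported associations, not on the planned primary analysis.

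**What to change.** In 2.11:

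- Present caries extent, tooth type and plaque on decayed surfaces descriptively by group, or compare them with a GEE with child as cluster. Description loses nothing, since randomisation already makes the null hypothesis of no systematic baseline difference true.
- Keep the chi-square tests, if wanted, for variables with one value per child.
- Use the GEE for all univariable and multivariable associations with arrest.
- Delete the logistic regression sentence, or restrict it to named child-level outcomes.

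The cost is the rewording of two sentences. Data, software and sample size stay the same.

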## Figures and Tables

**Figure 1 dentistry-11-00145-f001:**
[figure not shown]
The CONSORT flow diagram.

**Table 1 dentistry-11-00145-t001:** The schedule of enrolment, intervention, and assessments.

	STUDY PERIOD			
	Enrolment	Allocation	Post-Allocation	
TIMEPOINT	*−t* _1_	0	6 m	12 m
ENROLMENT:				
Eligibility screen	X			
Informed consent	X			
Allocation		X		
INTERVENTIONS:				
[Group A]		X	X	
[Group B]		X	X	
ASSESSMENTS:				
[Active caries]	X	X	X	X
[Arrested caries]			X	X

“X” means time point of each action.

**Table 2 dentistry-11-00145-t002:** Code for assessment of carious lesions (tooth surface level).

Carious Lesion	Code
Caries activity status	1: active, 2: arrested
Extent of caries lesion	1: distinct cavities, 2: extensive cavities
Presence of dental plaque	0: no, 1: yes
Non-vital signs (at tooth level)	0: no, 1: abscess/fistula, 2: pulpal involvement

**Table 3 dentistry-11-00145-t003:** Grouping of categorial variables of the parental questionnaire.

Variable	Group	Data Collection Period
Sex	Male Female	Baseline
Birthplace	Hong Kong Mainland China Other	Baseline
Serious systemic disease	Yes No	Baseline
Long-term medication	Yes No	Baseline
Monthly family income	HKD 20,000 or below HKD 20,001–40,000 HKD 40,001 or above	Baseline
Mother’s education level Father’s education level	Junior secondary school Senior secondary school Post-secondary or university	Baseline
Main caretaker	Parents Grandparents Maid or others	Baseline
Bottle-feeding before bed	Yes No	Baseline and 12-month follow-up
Sweet snack frequency	Less than once Once Twice More than twice	Baseline and 12-month follow-up
Daily tooth brushing	Yes No	Baseline and 12-month follow-up
Use of fluoride toothpaste	Yes No Not sure	Baseline and 12-month follow-up
Parents’ satisfaction for child’s dental appearance	Very satisfied Satisfied Dissatisfied Very dissatisfied	Baseline and 12-month follow-up
Parents’ satisfaction for child’s dental health	Very satisfied Satisfied Dissatisfied Very dissatisfied	Baseline and 12-month follow-up
Dental treatment during the last one year	Yes No	12-month follow-up
Category of the dental treatment	Check-up Fluoride treatment Filling Extraction Others	12-month follow-up

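### Parental satisfaction, one of the named secondary outcomes, has only a before-after McNemar test specified, so the randomised groups are not compared on it

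*Protocol article*

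**What the plan says.** Section 2.9.2 names parental satisfaction with the child's dental appearance and oral health, which "will be evaluated prior to the baseline examination and at the 12-month examination". The same section adds a second item: "The SDF treatment’s adverse effects will also be assessed after SDF application". Table 3 records both satisfaction questions on four ordered levels: "Very satisfied Satisfied Dissatisfied Very dissatisfied".

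Section 2.11 gives one sentence to the analysis of satisfaction: "The McNemar test will be used to investigate changes in parental satisfaction", with baseline and 12 months as the two time points. It does not mention treatment group.

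Three other statements in Section 2.11 could be thought to cover this outcome:

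- Chi-square: the "test will be conducted to assess the differences between the two intervention groups regarding their demographic background", and also baseline clinical features and oral health habits. Satisfaction is not in the list. The t-tests are for baseline VPI and dmfs.
- Generalized estimating equations: the model concerns the "effectiveness of post-treatment protocols in arrested caries after 12 months".
- Logistic regression: "A logistic regression model will be used to assess the associations between the outcomes and other potential factors". Neither satisfaction nor group is named.

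**The concern.** The trial randomises children to two post-treatment instructions so that the instructions can be compared. Every child in both arms receives 38% SDF at baseline and at 6 months (Section 2.8). A change in parents' satisfaction over 12 months therefore mixes the effect of SDF, the passage of time and any dental care obtained elsewhere. Only a contrast between the arms isolates the instruction, and the one test specified for satisfaction does not make that contrast.

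At stake is a secondary outcome reported from a randomised trial without using the randomisation. A significant before-after change could be read as evidence about the instructions when it is not. A real difference between arms could also go unseen.

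**Working it through.** **Structure of the test.** Reduce satisfaction to satisfied or dissatisfied. In an arm with n completers, let b be the number moving from dissatisfied to satisfied and c the number moving the other way. McNemar's test asks whether b and c differ, so it estimates the net change (b − c)/n.

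- Pooled over two equal arms, it estimates the average (ΔA + ΔB)/2.
- The trial's contrast is the difference ΔA − ΔB.
- If ΔA = +10 points and ΔB = −10 points, the average is (10 − 10)/2 = 0 while the difference is 20 points.
- Run within each arm, it tests ΔA = 0 and ΔB = 0 separately. Neither is a test of ΔA = ΔB.

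**Inputs for an illustration.** The plan gives no figure for satisfaction; its sample size is for caries arrest. From Section 2.10 come 127 children per group and 15% dropout: 127 × 0.85 = 107.95, so 108 completers per arm. The documents give no rate of change in satisfaction, so the following are assumptions: 20, 30 or 40% of parents change category, with net changes of 10 or 15 points.

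**Method.** 2,000 simulated trials per setting, exact McNemar at two-sided 0.05. The between-group test uses m = (b − c)/n and v = [(b + c)/n − m²]/n in each arm, and rejects when |mA − mB| / √(vA + vB) > 1.96.

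| Parents changing category | True net change, A / B | Pooled McNemar rejects | Between-group test rejects | Per-arm McNemar: one arm significant, the other not |
|---|---|---|---|---|
| 20% | +10 / −10 | 3.1% | 93% | 48% |
| 30% | +10 / −10 | 3.9% | 78% | 48% |
| 40% | +10 / −10 | 3.4% | 64% | 44% |
| 20% | +10 / +10 | 91% | 5.5% | 51% |
| 30% | +10 / +10 | 75% | 5.6% | 48% |
| 40% | +10 / +10 | 60% | 5.6% | 43% |

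Hand check of the second row: v = (0.30 − 0.01)/108 = 0.002685 per arm; standard error = √(2 × 0.002685) = 0.0733; 0.20/0.0733 = 2.73; power ≈ Φ(2.73 − 1.96) = Φ(0.77) ≈ 0.78. This agrees with the simulation.

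Opposite movement is the extreme case. With +15 points in A and none in B, pooled McNemar rejects in 68, 48 and 37% of runs at 20, 30 and 40% changing. Such a rejection still says only that satisfaction changed on average, not that the arms differ.

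**Per-arm results set side by side.** If the arms do not differ and each test has probability p of significance, exactly one is significant with probability 2p(1 − p): 2 × 0.05 × 0.95 = 9.5% at p = 0.05; 2 × 0.2 × 0.8 = 32% at p = 0.2 or 0.8; 2 × 0.5 × 0.5 = 50% at p = 0.5, the maximum.

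**The case against.** The strongest reply is that the test fits the question asked. The objective and null hypothesis (Sections 2.1 and 2.2) confine the randomised comparison to caries arrest. The abstract speaks of satisfaction with SDF therapy, not with the instruction, and Section 2.11 says the test is for changes. McNemar's test is valid for paired change. On this view, what remains is an omission of the kind a condensed article leaves to a fuller document.

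Part of this stands: a before-after description is legitimate, and no passage states a between-group aim for satisfaction. But satisfaction is listed as an outcome of a two-arm randomised trial, and the article does state its analysis. The stated analysis leaves out the randomised factor, which is more than missing detail.

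A second reply is that the logistic regression refers to outcomes in the plural, while arrest has its own clustered model, so satisfaction may be included there. The sentence can be stretched that far. It names neither satisfaction nor group, so it does not clearly supply the comparison.

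Several stronger readings are tempting, but the documents do not support them:

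- That satisfaction is the sole secondary outcome. Adverse effects stand under the same heading.
- That the plan will run McNemar in each arm and compare p-values. It does not say so; the 2p(1 − p) figures describe a misuse to avoid, not a stated procedure.
- That the four-level scale makes the test unusable. A stated cut, or the McNemar-Bowker extension, would resolve that, though neither adds a group comparison.
- That staining by SDF drives the before-after change. The documents do not say that SDF stains lesions; Section 2.5.2 lists discoloration only as an item to record. The argument needs only that both arms receive SDF.

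**Conclusion.** The point holds in a limited form. As written, Section 2.11 specifies no clear comparison of Group A with Group B on parental satisfaction, and the one test it specifies cannot provide one. This conclusion is structural and needs no numerical assumption. The simulated figures only show how far a before-after test and a between-group test can diverge. They rest on a binary cut, 108 completers per arm, and assumed rates and directions of change. The plan should be amended on this point. The primary outcome, its analysis and the sample size are untouched.

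**What to change.** Add to Section 2.11 a between-group comparison of 12-month satisfaction, with appearance and oral health analysed separately. Use proportional-odds regression on the four levels, with randomised group, baseline satisfaction and the caries stratum used in randomisation (Section 2.7) as terms. Binary logistic regression with a prespecified satisfied/dissatisfied cut would also serve. Report the group odds ratio with its 95% confidence interval. Keep the before-after McNemar or McNemar-Bowker results as description, and say that they do not compare the groups.

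The cost is about one sentence. Table 3 already schedules both items at baseline and 12 months, so no new data are needed.
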